### 3c. Interventions

Intervention group: Patients in the intervention group receive minimum five educational sessions over 6 weeks (i.e., about weekly) as an integrated prehabilitation program tailored to meet the

individual patient's need for risk reduction at surgery, see Table 2 and 3. It is introduced via the surgical 'Engage in the process of change'. The smoking intervention follows the Gold Standard Programme GSP, which has been translated to the standardized alcohol cessation intervention, exercise training programme, and nutritional intervention.

Project nurses from the participating centre, who have taken part in a 5-day educational program followed by practical training in the Gold Standard Programme (GSP), provide the intervention. The project leader ([name]) of the trial ensures that counsellor follows the principles of the GSP program by regular discussion of the intervention.

Table 2. Weekly sessions after inclusion (Preop: preoperatively)

|                                  | Week 1 | Week 2 | Week 3 | Week 4 | Week 5 | Week 6 Follow-up
+ continued preop. |
|----------------------------------|--------|--------|--------|--------|--------|----------------------------------------|
| Smoking cessation                | X      | X      | X      | X      | X      | X                                      |
| Nutrition program (malnutrition) | X      | X      | X      | X      | X      | X                                      |
| Nutrition program (obesity)      | X      | X      | X      | X      | X      | X                                      |
| Alcohol cessation                | X      | X      | X      | X      | X      | X                                      |
| Physical Activity                | X      | X      | X      | X      | X      | X                                      |

Table 3. The patient education program in the Gold Standard Programme (GSP)

| Week number                | Education subject                                              |
|----------------------------|----------------------------------------------------------------|
| 1 (at inclusion)           | Level of motivation, ambivalence, pros and cons (see Appendix) |
| 2                          | Dependence, withdrawal symptoms (experience and expectations)  |
| 3                          | Relapse (description and management)                           |
| 4                          | Benefits of short- and long-term lifestyle change              |
| 5                          | Continued change of lifestyles (handling risk of relapse)      |
| 6 and follow-up            | Continued education based on the current conditions            |
| + continued preoperatively | Continued education based on the current conditions            |

At each meeting we look into: The status and follow-up on the 'homework' via logbooks as well as challenges and successes. Patients are asked if they have experienced side effects of the pharmacological support. Potentially unknown side effects are reported and, if serious, may lead to early termination of the trial.

The specific physical activity includes 5 minutes respiratory exercise and 25 minutes activities chosen by the patient from a menu, thus adding up to 30 minutes per day. It starts on the first meeting and the patient walks through the complete 30 minutes program supported by the counsellor.

The specific nutrition program is adjusted to the patients individual need ensuring the complete intake required to change lifestyle in accordance with the individual needs.

The pharmaceutical support for smoking cessation intervention follows the national recommendations that have successfully been used in Danish studies of surgical patients. It is emphasized that the entire program is adapted to the individual patients - including guidance on supportive medicine - and that all pharmaceutical support is an offer. It includes personalised Nicotine Replacement Therapy (NRT) in accordance with the internationally acknowledged Fagerström test for nicotine dependency and patient preferences. Pharmaceutical support for risky drinkers also follows the national recommendations, successfully been used in Danish studies of surgical patients. It includes thiamine (300 mg daily) and combined B vitamins, alcohol withdrawal prophylaxis and treatment (chlordiazepoxide 10 mg as required in national guidelines) and low dose of disulfiram (200 mg × 2 weekly) supervised at weekly meetings (administered only if the patient has a negative alcohol breath test). The study medication is provided for free. The intervention group is followed during the intervention by additional measurements, Table 4.

Table 4: Additional measurements in the intervention group related to the SNAP factors of the individual participants (AUD: Alcohol use disorder; AWS: Alcohol withdrawal symptoms; CIWA-aR: Clinical Institute Withdrawal Assessment for alcohol-revised; CO: carbon-monoxide; Diagnostic NRT: nicotine replacement therapy; TLFB: timeline-follow-back)

| Measurements
(Intervention group, exclusively) | Week1 | Week 2 | Week 3 | Week 4 | Meet 5 | Week 6+ |
|---------------------------------------------------|-------|--------|--------|--------|--------|---------|
| Motivation and reflections                        | X     |        |        |        |        |         |
| Adverse events                                    | X     | X      | X      | X      | X      | X       |
| Smoking                                    |       |        |        |        |        |         |
| Cigarettes per day (N°)                           | X     | X      | X      | X      | X      | X       |
| Tobacco dependence (Fagerström criteria)          | X     |        |        |        |        |         |
| Use of NRT (mg)/other craving reducing medicine   | X     | X      | X      | X      | X      | X       |
| Validation by CO concentration (breath)           | X     | X      | X      | X      | X      | X       |
| Nicotine biomarkers in urine                      | X     |        | X      |        | X      | X       |
| Alcohol                                    |       |        |        |        |        |         |
| Alcohol per week (units 12 g, TLFB)               | X     | X      | X      | X      | X      | X       |
| Alcohol dependency (AUD criteria)                 | X     |        |        |        |        |         |
| Alcohol concentration (breath test)               | X     | X      | X      | X      | X      | X       |
| Alcohol biomarkers (blood + urine)                | X     |        | X      |        | X      | X       |
| If withdrawal symptoms (CIWA-aR)                  | X     | X      | X      | X      | X      | X       |
| Use of AWS prophylaxis (mg)                       | X     | X      | X      | X      | X      | X       |
| Nutrition                                  |       |        |        |        |        |         |
| Food intake according to plan                     | X     | X      | X      | X      | X      | X       |
| Weight and bio-impedance                          | X     | X      | X      | X      | X      | X       |
| Validation by Nutrition profile (blood)           | X     |        | X      |        | X      | X       |
| Physical Activity                          |       |        |        |        |        |         |
| Physical activity according to plan               | X     | X      | X      | X      | X      | X       |
| Steps walked per day                              | X     | X      | X      | X      | X      | X       |
| Walking test                                      | X     |        | X      |        | X      | X       |
| Hand grip strength                                | X     |        | X      |        | X      | X       |

Control group: All patients in the control group receive the project information about the study. They receive the routines of the involved departments (e.g., smokers may receive the Very Brief Advise and referral to a municipal clinic for smoking cessation intervention). All patients are free to use any support offered outside the project, including the free access to lifestyle intervention in their municipality.

All participants: All meetings are planned in connection with scheduled visits in the outpatient clinic or at admission to hospital when possible and in other cases the transportation for the weekly meetings will be reimbursed. All participants have telephone access to the research nurse during the project.

All receive routine procedures on general patient information, thromboembolic prophylaxis and antibiotics, anaesthesia, surgical intervention, and postoperative care as used at the centre. All patients are evaluated at inclusion and 6 weeks after/at surgery as well as 1, 3 and 6 months postoperatively, Table 1.

To find out if eligible patients who decline to participate in the trial differ from those enrolled, we ask for permission to follow them perioperatively via the medical records and for 2 years in the health registries. Those who accept are asked to provide informed consent.

### 4. Statistical considerations: Power calculation

The power calculation is based on the literature as presented above, thus aiming at halving of postoperative complications after intensive programs for smoking, alcohol, and malnutrition. The impact of physical activity is lower, and obesity is sparsely investigated but targeting co-existing SNAP like STRONG should increase the effect due to interactions. Therefore, the main hypothesis is clinically relevant. For ventral hernia in high-risk patients, STRONG would expectantly half the overall complication rate from conservatively 20% to 10%. When using 80% power and 2 x alpha=0.05 we get 2 x 199 participants. This also covers the secondary outcomes regarding lifestyle improvements and costs.

In case of dropping out, the patients are asked to allow follow-up via the medical record system and a telephone interview. It is our experience from previous studies that 90% the drop-out patients accept this. Therefore, the development of complications as the primary outcome will be available for close to all randomised patients. We use block randomisation in rather small groups, which would only to a minimal degree impact the distribution between the intervention and control groups.

In study 4 the prevalence of risky SNAP factors on all patients that potentially could be screened for eligibility in study 1 (about 2 x the included numbers = 800 patients) will be reported as frequencies and 95% CI and analyzed for the potential maximum risk reduction and effects, if they would have received a related STRONG intervention. If possible, the potential will be analyzed for the most frequent combined risk factors.

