### Brief Summary (English)

This national project is the first to include all SNAP factors (Smoking, Nutrition - both obesity & malnutrition - Alcohol, and Physical activity) in a combined intervention aiming at risk reduction for patients scheduled for ventral hernia repair. It will generate new knowledge of the effect on risk reduction via intensive lifestyle intervention 4 weeks prior to surgery.

The overall goal is to reduce the inequity in health via perioperative STRONG lifestyle intervention aiming at a better health gain by surgical risk reduction at short time and improved health on longer time. In total, 2x200 surgical patients disadvantaged by preoperative risky lifestyle will participate.

The primary outcome is postoperative complications. Other important outcomes are clinically relevant lifestyle improvements, frailty and comorbidity symptoms, patient motivation and reflections, health-related quality of life and cost-effectiveness on short and longer time. In addition, possible dose responses between lifestyle at surgery and complications, health & costs, and association between self-reported and validated lifestyles.

This project builds further on the ongoing and smaller STRONG-Cancer project for risk reduction at surgery with change in lifestyle as the primary outcome, approved in 2020 (H-20081571; P-2020-95).

Collaboration among:

4 Surgical Departments at:

HERLEV Hospital ([name]), HORSSENS

Regional Hospital ([name]), Zealand

University Hospital KØGE

([name]), and

Holbæk Hospital ([name])

and

The Danish Centre for Health

Economics at University of

Southern Denmark ([name])

and

The STRONG Team at WHO-

CC, Parker Institute at

Bispebjerg-FREDERIKSBERG

Hospital ([name])

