### **2c) STRONG-Hernia is powered for evaluation for postoperative complications**

A prior step towards the present STRONG-Hernia project has been taken by the ongoing STRONG – Cancer project, in which we are evaluating the effect of the STRONG program on lifestyle improvement and related risk reduction, exclusively from improvement of SNAP factors. STRONG-Cancer is an RCT recruiting a smaller group of patients scheduled for urothelial cancer surgery after preoperative neoadjuvant therapy. In a nested interview study, we collect the preferences among the recruited patients, their relatives, and staff (www.clintrials.gov NCT04088968; the Danish Scientific Ethical Committee H-20081571; the Danish Data Protection Agency P-2020-95). That trial does not aim at and therefore is not powered for evaluation on postoperative complications, health, and cost-effectiveness, like the present STRONG-Hernia project.

However, the positive process is useful for the present project on ventral hernia repair. Thus, the present project on ventral hernia repair is not a repetition of another project but adds completely new and clinically important knowledge to the research area of prehabilitation regarding SNAP factors.

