### Analyses

Analyses are done blinded as Intention-to-Treat (ITT). We will use Fisher's exact test for frequencies, Mann-Whitney for continuant variables, and  $p < 0.05$  is chosen for statistical significance. To benefit future meta-analyses, we will also give the parametric results. This would also meet the tradition that costs are usually reported with means and standard error (SE), mean difference (MD), and 95% confidence interval (CI). Bootstrapping procedures are used to calculate the cost-effectiveness plane and the acceptability curve by repeatedly resampling the data (1,000 incremental cost and effect pairs). Sensitivity analyses will be performed for differences in local standards for the control groups among the surgical centres. Analyses as per-protocol, dose-response, prediction, sensitivity, and the other secondary analyses are done by logistic regression models including control for confounders and effect-modifiers and reported as Risk Rates with 95% Confidence Interval (CI). The results are considered significant if the CI does not involve 1.00.

Absolute (ARR) is calculated as the events in the control group minus the events in the intervention group, and the relative risk reduction as the ARR divided by the events in the control group. The number needed to treat was calculated by  $1/ARR$ . We will present the mortality as Kaplan-Meier plots and test by the log rank test.

In case of dropouts, the primary outcome is collected from the medical record and a telephone follow-up after acceptance from the patient. In case of missing health data, the lifestyle at baseline will be imputed as the results in order not to over-estimate the results of changing lifestyle. This would expectantly impact the results to a similar degree in both groups.

All quantitative analyses are performed in SPSS Statistics® version 22.

The qualitative analyses are done using Kirsti Malterud's approach of systematic text condensation.

After import into NVivo® qualitative data analysis software version 11, the systematic text condensation in the four steps takes place: 1) Total impression of all answers and identifying preliminary themes, 2) coding by identifying and sorting meaning units, 3) condensation into code groups, and 4) synthesising the condensates into a story grounded in the empirical data.

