### Outcomes and data collection (Table 1)

Postoperative complications (within 1, 3, 6 months after surgery): The primary outcome is the number of patients with > 1 complication, defined by requiring documented treatment, categorized in accordance with the Clavien-Dindo grading and the Comprehensive Complication Index (CCI). They include adverse events and side effects. Secondly, length of stay, second surgery, revisits and – admissions at hospital, visits in primary care, time back to work or previous activities.

Successful risk reduction at follow-up/at surgery: Defined as SNAP below risk level validated as described in chapter 2; for obesity BMI < 30 or at least 5% and max 10% loss of body fat mass preoperatively (0.5–1 kg/weekly without developing malnutrition). Data are collected via logbook and validation.

For frailty: In addition to pI-protein, the frailty level (0-5, 0 is best) is measured by Fried's Modified Frailty Score according to Blammers as that is associated with development of complications. It includes five criteria:

- Slowness: Performance time in the walking test,
- Weakness: Hand grip strength measured by a dynamometer,
- Exhaustion: Responding "All the time" or "Often" to the item "I feel everything is an effort / I can't get going" in the Hospital Anxiety & Depression Scale.
- Weight loss: Self-reported 5 kg over the last year
- Low activity: Below 3 MET

Health (at baseline, after 6 weeks/at surgery, and 6 months postoperatively): This is measured by the health-related quality of life measured by EQ-5D with 5 dimensions and the overall health measured with a scale from 0 to 100 with a higher score representing a better health. Within 2 years of follow-up, the morbidity is measured as visits and stay at hospital as well as visits in primary care and prescribed medicine and grouped diagnoses groups as well as mortality.

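### The 2 x 199 sample size matches an uncorrected two-proportion formula, but the protocol analyses with Fisher's exact test, which gives about 77–80% power; the claim that the size also covers costs has no stated basis

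*Protocol*

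**What the plan says.** Section 4 expects STRONG to "half the overall complication rate from conservatively 20% to 10" per cent and continues: "When using 80% power and 2 x alpha=0.05 we get 2 x 199 participants". It names no test or formula. The Brief Summary rounds the size up: "In total, 2x200 surgical patients disadvantaged by preoperative risky lifestyle will participate".

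The Analyses part of section 3a assigns Fisher's "exact test for frequencies, Mann-Whitney for continuant variables". The outcomes section makes the primary endpoint a count of patients: "The primary outcome is the number of patients with > 1 complication, defined by requiring documented treatment". It is therefore a binary outcome per patient, and Fisher's test is the one that applies to it.

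There is no inflation for missing outcomes. Section 4 relies on follow-up of dropouts through records and telephone: "It is our experience from previous studies that 90% the drop-out patients accept this".

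On other outcomes, section 4 adds: "This also covers the secondary outcomes regarding lifestyle improvements and costs". Section 2c says that the cancer trial is not "powered for evaluation on postoperative complications, health, and cost-effectiveness, like the present STRONG-Hernia project", which presents the hernia trial as powered for those outcomes.

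**The concern.** A power statement holds only for the test that will be used. Fisher's exact test is conservative in 2 x 2 tables of this size: its actual type I error lies below 5%, and it loses power accordingly. If 199 per arm came from a formula without that penalty, the protocol's own test does not deliver the protocol's own 80%. The planned 400 patients are only two more than 2 x 199, so almost no margin absorbs the difference.

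The cost statements raise a different problem. Telling readers that a comparison is powered invites them to take a non-significant result as evidence of no difference. With no inputs behind the statement, that reading would have no foundation.

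**Working it through.** **Inputs, all from the Protocol.** Control rate 20%, intervention rate 10%, 80% power, two-sided alpha 0.05 (section 4); 200 per arm planned (Brief Summary); Fisher's exact test for frequencies (section 3a, Analyses).

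**Step 1: reproduce 199.** The pooled-variance formula without continuity correction, with mean rate 0.15, is

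n = [1.96 × √(2 × 0.15 × 0.85) + 0.8416 × √(0.20 × 0.80 + 0.10 × 0.90)]² / 0.10²

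= (0.9897 + 0.4208)² / 0.01 = 198.96, so 199 per arm.

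Other formulas with the same inputs do not give 199:

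| Formula | n per arm |
|---|---|
| Unpooled variance | 197 |
| Average-rate variance | 201 |
| Arcsine | 195 |
| Continuity-corrected | 219 |
| Pooled, one-sided | 157 |

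The document does not say which formula was used. The exact match points to the pooled uncorrected one, which corresponds to the uncorrected chi-square test.

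**Step 2: power of the planned test.** All pairs of binomial outcomes were enumerated under 20% and 10%. The probabilities of the tables that each test rejects at two-sided 0.05 were then summed.

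| Arms (control:intervention) | Fisher's exact | Uncorrected chi-square |
|---|---|---|
| 199:199 | 76.6% | 80.9% |
| 200:200 | 76.8% | 81.1% |

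At the same size, the uncorrected chi-square test delivers the stated 80% and Fisher's does not, so the gap comes from the choice of test. With equal arms, Fisher's test first reaches 80% at 214 per arm (213 gives 79.9%, 214 gives 80.1%).

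**Step 3: unequal arms.** Fisher's power dips when the arms are exactly equal. With 400 patients in total, it is 78.1% at 201:199, 79.5% at 199:201, 79.3% at 202:198 and 80.0% at 203:197. Every unequal split from 192:208 to 208:192 gives 77.9% to 80.0%. Against the stated 80%, the shortfall therefore runs from about 3 points (80 − 76.8 = 3.2) to almost nothing.

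**Step 4: type I error.** With a common rate of 15% and 200 per arm, the actual size is 3.6% for Fisher and 5.1% for the uncorrected chi-square.

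**Step 5: costs.** The document gives no cost difference, SD or power, so nothing can be recomputed. For scale only, with 199 per arm and a normal comparison of means, the difference detectable with 80% power is (1.96 + 0.8416) × √(2/199) = 0.28 SD. If the cost SD is assumed to be 1 to 2 times the mean cost, that is 28% to 56% of the mean. Whether such a difference is plausible cannot be judged from the document. The same sentence in section 4 asserts coverage of lifestyle improvements, also without inputs.

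**The case against.** The strongest reply is that nothing is wrong with the arithmetic. The figure of 199 reproduces, and sizing with the normal formula while analysing with Fisher's test is a common approximation. The difference is also small beside the uncertainty in the assumed 20% control rate. This stands as to size, but the two statements still disagree within one protocol and a wording change removes the conflict.

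A second reply is that about 77% describes only exactly equal arms. Randomisation is stratified by four centres and three SNAP-count levels, which makes 12 strata, with blocks of 2 to 5. Incomplete blocks make an exact 200:200 split unlikely. This also stands: a reader might infer that the true power is simply 77% and the flaw serious, but the range is about 77–80%.

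A reader might also infer about 75% power from 5% missing outcomes (74.7% at 190:190). The 5% is an assumption that no figure in the document supports; section 4 expects outcomes for nearly all patients.

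The most tempting stronger reading is that the trial is too small for costs. Suppose each complication costs C, so that the expected saving is 0.10C, and let s be the SD of all other costs. With 200 per arm, SE = √[(0.16C² + 0.09C² + 2s²)/200]. Power is then 81% for s = 0, 52% for s = 0.35C and 25% for s = 0.7C. These values of s are invented. The bound this suggests, that cost power cannot exceed complication power, holds only if every complication costs the same and STRONG changes incidence alone. The protocol grades severity, and its background cites fewer patients with three or more complications after a related intervention. If STRONG also cut the cost per complication by an assumed 30%, power at s = 0.35C would be 78%. Inadequacy for costs is therefore not shown.

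**Conclusion.** The point holds at modest size. The stated 80% corresponds to an uncorrected two-proportion comparison. With the Fisher test that the protocol names, power is 76.6% at 199:199, 76.8% at 200:200 and about 78–80% for slightly unequal splits of 400. This rests on the protocol's own 20% and 10%, on outcomes for all patients, and on Fisher's test being the primary analysis, as section 3a implies. That the size came from the uncorrected formula is inferred from the exact match, since section 4 names none. The power figures do not depend on that inference.

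The statements that the size covers costs and cost-effectiveness are unsupported. It does not follow that they are false. Neither point threatens the validity of the trial or calls for more patients.

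**What to change.** For the primary outcome, replace Fisher's exact test in section 3a with a named chi-square or score-type test. The preferable choice is Cochran-Mantel-Haenszel stratified by the randomisation factors, centre and SNAP count. Fix it before any outcome data are seen, because a later move to a less conservative test could look data-driven. The downside is a type I error of about 5.1%, marginally above nominal, where Fisher's is about 3.6%. Both figures, and the 81% power, are for the unstratified comparison with equal arms.

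Otherwise, keep Fisher and state in section 4 that power is about 77–80%, depending on the balance of the arms. In either case, name the formula behind 199.

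Separately, delete the statement in section 4 that the size also covers costs, and the implication in section 2c that the trial is powered for cost-effectiveness. Present costs as estimates, using the mean differences with 95% confidence intervals and the bootstrap analysis already planned in section 3a.

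The cost is wording only: no extra patients, and no change to data collection.
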